## Abstract

**Background:**

Transgender women in the United States experience numerous risk factors for HIV acquisition and transmission, including increased rates of homelessness, alcohol and drug use, sex work, and nonprescribed hormone and soft tissue–filler injections. In addition, transgender women face discrimination and social/economic marginalization more intense and deleterious than that experienced by lesbian, gay, or bisexual individuals, further worsening health outcomes. Although little research has been done specifically with young transgender women aged 35 years and younger, existing evidence suggests even further elevated rates of homelessness, substance use, and engagement in HIV transmission risk behaviors relative to their older transgender women and nontransgender young adult counterparts. Young transgender women living with HIV experience a range of barriers that challenge their ability to be successfully linked and retained in HIV care.

**Objective:**

The aim of this randomized controlled trial, *Text Me, Girl!*, is to assess the impact of a 90-day, theory-based, transgender-specific, text-messaging intervention designed to improve HIV-related health outcomes along the HIV care continuum among young (aged 18-34 years) transgender women (N=130) living with HIV/AIDS.

**Methods:**

Participants were randomized into either Group A (immediate text message intervention delivery; n=61) or Group B (delayed text message intervention delivery whereby participants were delivered the text-messaging intervention after a 90-day delay period; n=69). Over the course of the 90-day intervention, participants received 270 theory-based text messages that were targeted, tailored, and personalized specifically for young transgender women living with HIV. Participants received 3 messages per day in real time within a 10-hour gradual and automated delivery system. The text-message content was scripted along the HIV care continuum and based on social support theory, social cognitive theory, and health belief model. The desired outcome of *Text Me, Girl!* was virological suppression.

**Results:**

Recruitment began on November 18, 2016, and the first participant was enrolled on December 16, 2016; enrollment closed on May 31, 2018. Intervention delivery ended on November 30, 2018, and follow-up evaluations will conclude on August 31, 2019. Primary outcome analyses will begin immediately following the conclusion of the follow-up evaluations.

**Conclusions:**

Text messaging is a communication platform well suited for engaging young transgender women in HIV care because it is easily accessible and widely used, as well as private, portable, and inexpensive. *Text Me, Girl!* aimed to improve HIV care continuum outcomes among young transgender women by providing culturally responsive text messages to promote linkage, retention, and adherence, with the ultimate goal of achieving viral suppression. The *Text Me, Girl!* text message library is readily scalable and can be adapted for other hard-to-reach populations.

**International Registered Report Identifier (IRRID):**

DERR1-10.2196/12837

## Introduction

As a population, transgender women bear a disproportionate burden of HIV/AIDS and other health disparities. In the United States, transgender women experience numerous risk factors for HIV acquisition and transmission [1-3], including increased rates of homelessness [4-6], alcohol and drug use [6,7], and sex work [7,8]. In addition, many transgender women use nonprescribed hormone injections and/or medically unsupervised soft tissue–filler injections, HIV risk factors that are specific to this population [5,9,10]. Furthermore, transgender women face discrimination and social/economic marginalization more intense and deleterious than that experienced by lesbian, gay, or bisexual individuals [4], further worsening expected health outcomes [11-13].

Although HIV surveillance data are often not collected for transgender persons in the United States [14], meta-analytic and aggregated jurisdictional data suggest that HIV prevalence rates among transgender women are an order of magnitude higher than the US general population (18.4%-30.6% [7,15] vs 0.3%-0.4% [16]), with the odds of becoming HIV-positive estimated to be 34.2 times higher for transgender women than other US adult populations [15]. Within Los Angeles county (LAC), there is a stark disparity such that transgender women exhibit the second highest estimated HIV prevalence rate of any priority group (16.7%), marginally lower than the prevalence for men who have sex with men (MSM) (18.4%) [17]. A community-based convenience sample of transgender women in LAC evidenced an increase in self-reported HIV prevalence of close to 60% over a 17-year period, from 22% in 1998-1999 to 35% in 2015-2016 [18]. Although transgender women make up only 0.1% of the general population in LAC, they represent 1.3% of all people living with HIV (PLWH) and 1.4% of recent diagnoses from 2009 to 2013 [19]. A study found that more than half of the respondents reported recent homelessness, less than a third were employed, more than two-thirds reported doing sex work in the past 3 months, 85% reported HIV transmission risk behaviors, and 20% were HIV-positive [20]. As a result, transgender women have a nearly 7 times higher likelihood in delaying medical care after an HIV-positive diagnosis than cisgender women [21]. Multilayered stigma, accompanied by an inability to pay for care and misinformation about both the need for antiretroviral therapy (ART) and/or the existence of ART/hormone therapy interactions, often contributes to low linkage to and retention in care outcomes among young transgender women [22,23].

With the high HIV prevalence rate among transgender women, it is necessary to develop interventions to improve linkage to ART and address the multitude of barriers experienced by transgender women to enhance their retention in HIV care. A potential solution to improve adherence and retention among transgender women is through mobile phone text messages. Several studies have found success in improving health services and outcomes through the use of text message interventions with PLWH [24-28]. In 2014, internet and mobile phone use among people in the United States aged 12 to 29 years was over 90% [29]. Unlike internet-based social media platforms, text messaging is easily accessible, private, portable, inexpensive, and used daily by nearly all the youth and the young adults in the United States, including the most vulnerable transgender women [30-32]. Text messaging is an appropriate modality for reaching young transgender women because this population regularly uses text messaging and social media platforms to gain positive perspectives on their gender identity, develop Web-based communities, gather health information, purchase gender-confirmation hormones, and acquire sex partners [33-36].

In regard to HIV care, a study with PLWH found that a personalized daily text message reminder improved participants’ adherence to ART compared with those who received a beeper reminder [24]. Likewise, in another trial, youth living with HIV who had poor adherence reported better self-management of their HIV medication after 3 months when receiving culturally relevant and motivational daily text messages [27]. Given the rapid increase of mobile phone use and its accessibility to transgender women, it is important to understand the significance of text message use in facilitating HIV care among this high-risk population. Therefore, the purpose of this study was to determine whether providing culturally responsive text messages that promote healthy living and linkage, retention, and adherence may help young transgender women living with HIV in LAC be successfully linked and retained in HIV care with the ultimate goal of viral suppression.

## Methods

### Study Design

*Text Me, Girl!* was a randomized controlled trial to assess the impact of a 90-day theory-based, transspecific, text-messaging intervention designed to improve health outcomes along the HIV care continuum, with the desired outcome of viral suppression among HIV-positive young transgender women (Figure 1). The HIV care continuum is a model used to identify gaps in HIV services and develop strategies to improve engagement in care among PLWH. The HIV care continuum outlines sequential stages as follows: diagnosis of HIV infection, linkage to care, retention to care, adherence to ART therapy, and achievement of viral suppression [37]. All study procedures were approved by the Friends Research Institute (FRI) Institutional Review Board and the Western Institutional Review Board.

During the 90-day intervention period, participants received 3 scripted, theory-based, transspecific text messages per day (270 text messages total), which were targeted, tailored, and personalized. The *Text Me, Girl!* text message library was adapted from a larger library of 616 messages originally developed for a study with methamphetamine-using MSM [38].

**Figure 1 figure1:**
[figure not shown]
*Text Me, Girl!* study design. f/u: follow-up; HRSA: Health Resources and Services Administration; mo: month.

Only the messages related to the HIV care continuum were modified: (1) HIV positivity/physical and emotional health, (2) linkage/retention in HIV care, and (3) ART medication adherence/viral load suppression. The text message library was tailored specifically to the needs of young transgender women living with HIV in terms of verbiage and content. The text message library was personalized in that participants could customize their 10-hour delivery timeframe, that is, intervention time period, and could personalize their delivery platform to their mobile phone or an email inbox. Several iterations occurred; the first level of modifications was made with 4 young adult transgender service providers who were given the original text-message library to adapt for young adult transgender women living with HIV. Following several revisions, the library was brought before the transspecific Community Advisory Board for the second level of modifications. The Community Advisory Board is multicultural and comprised both transgender women living with HIV and HIV-negative transgender women, program consumers, gatekeepers and stakeholders, service providers from local community-based organizations that provide services to transgender women, and members of local community planning and advocacy groups (eg, LAC Commission on HIV, Transgender Service Providers Network, and Transgender Task Force). The Community Advisory Board members reviewed and discussed every message in detail. Following the adaptation into a culturally responsive text-message library for young adult transgender women living with HIV, the research team reviewed each message and, if necessary, made minor modifications to ensure that each message had a theoretical foundation.

Text messages were based on, and equally distributed across, 3 behavioral theories: social support theory [39,40], social cognitive theory [41,42], and health belief model [43]. Social support theory encompasses instrumental, emotional, and informational supports, which have been shown to reduce stress and improve health outcomes [40,44,45]. Social cognitive theory serves to increase individuals’ self-efficacy and help develop self-regulation skills [42,46]. As low self-esteem has been associated with increased HIV risk among gender/sexual minority populations [47], increased self-esteem can serve to optimize HIV care outcomes. Health belief model states that threats to health can increase one’s likelihood of engaging in protective health behaviors [43]. Table 1 illustrates how the text message library was developed to have both a theoretical foundation and be transgenderculturally responsive.

Text messages were transmitted through gradual automation administration every day including weekends, in real time, within a 10-hour period. The automated text message delivery system was developed specifically for this study by Qualtrics, a digital survey development and administration company. Thus, participants received a text message every 5 hours (eg, at 12:00 pm, at 5:00 pm, and at 10:00 am). Each text message was unique, so participants did not receive the same scripted text message twice. The intervention was designed to be cost-efficient, sustainable, and easily scaled by community agencies throughout the United States.

### Ethical Approval

All procedures performed in studies involving human participants were in accordance with the ethical standards of the institutional and/or national research committee and with the 1964 Helsinki declaration and its later amendments or comparable ethical standards.

### Informed Consent

Informed consent was obtained from all individual participants included in the study.

**Table 1 table1:** Sample *Text Me, Girl!* theory-based and transspecific text message library.

HIV care continuum	General message	Transspecific message	Theoretical foundation
HIV positivity/physical and emotional health	Take care of yourself.	Trans pride is taking care of yourself.	Social support theory
Linkage/retention in HIV care	See your doctor.	Protect your trans beautiful body, see your doctor.	Health belief model
Antiretroviral therapy medication adherence	Take your meds.	Take your meds, girl! You can do it!	Social cognitive theory

### Sample

The study inclusion criteria were as follows: gender identity as a woman, assigned a biological sex of male at birth, aged between 18 and 34 years, confirmed HIV-positive serostatus, ability to receive daily text messages on either a personal mobile phone or via an email account, tested HIV positive for the first time within the last 12 months or had not had an HIV care visit in the previous 6 months or had a viral load of ≥200 copies/mL on her last lab test result or not currently prescribed ART medication or was currently prescribed ART medication but did not rate her ability to take all her medications as excellent, willing and able to provide informed consent, and willing and able to comply with study requirements. Individuals were excluded if they did not meet all the eligibility criteria.

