#### Random Assignment

After completing the baseline assessment, participants were assigned to a condition through an urn randomization procedure. The urn randomization procedure provided balance across age (18-24 and 25-34 years), race/ethnicity (Latino/Hispanic and all other race/ethnicities), and HIV care continuum status (linked, nonlinked to HIV care). Participants were randomized into 1 of the 2 conditions: Group A—immediate text message intervention delivery (n=61) or Group B—delayed text message intervention delivery (n=69) whereby participants were delivered the text-messaging intervention after a 90-day delay period. Both groups received the same 90-day text-messaging intervention. The randomized 2-group repeated measures design assessed participants at 3, 6, 12, and 18 months post randomization.

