### Statistical Analyses

Table 2 provides all evaluation outcomes and their chosen measurement models. Power calculations are based on assumptions of alpha=.05 (2-tailed tests), a sample size of 130 HIV-positive young transgender women, and a power standard of 0.80. It was calculated that logistic regression analyses of primary outcomes would be able to find a minimum detectable odds ratio of 2.98 for linkage/uptake of ART and achievement of an undetectable viral load (the primary outcomes of interest).

**Table 2 table2:** Study outcomes and measurement models.

Primary outcome	Measurement model
Linkage to HIV primary care (self-report and EMR^a^/EHR^b^ abstraction)	0= Participant did not attend HIV medical visit within 3 months of enrollment; 1= Participant attended within the first 3 months
Prescribed ART^c^ medication (self-report and EMR/EHR abstraction)	0=Participant is not prescribed HIV medication; 1=Participant is prescribed HIV medication
Retention in HIV primary care (self-report and EMR/EHR abstraction)	0=Participant did not attend a second HIV care appointment after the initial 3 months; 1=Participant attended an additional HIV primary care visit after the initial 3 months
ART adherence (self-report)	Ordinal scale (Likert)
Viral load monitoring (self-report and EMR/EHR abstraction)	Binary (0=>200 copies/mL, 1=<200 copies/mL)

^a^EMR: electronic medical report.

^b^EHR: electronic health report.

^c^ART: antiretroviral therapy.

All regression analyses assess assumptions of normality and model fit. In addition to the primary outcomes listed in Table 2, participants were assessed for changes in their HIV-related self-efficacy from baseline to follow-up evaluations. The HIV-ASES scale was used to assess HIV self-efficacy, producing continuous values suitable for ordinary least squares (OLS) regression. In addition, if during implementation, a sufficient number of participants opted in to receive one or more of the postintervention retention/engagement text messages available through final distal follow-up evaluation, additional analyses were carried out to estimate the observed effect(s) of receiving these postintervention text messages.

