## Discussion

*Text Me, Girl!* was designed to meet the needs of underserved young transgender women living with HIV/AIDS. Young transgender women living with HIV experience a range of barriers that challenge their ability to be successfully linked and retained in HIV care. Text messaging is a communication platform well suited for engaging young transgender women in HIV care because it is easily accessible, widely used, private, portable, and inexpensive. *Text Me, Girl!* aimed to improve HIV care continuum outcomes among young transgender women by providing culturally responsive text messages to promote linkage, retention, and adherence, with the ultimate goal of achieving viral suppression. The *Text Me, Girl!* text message library is readily scalable and, if successful, can be adapted for application with other hard-to-reach populations.

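### Women already suppressed and on ART can enter, yet ART uptake and achievement of suppression are powered on all 130 and scored as current status, with no baseline viral-load or ART term named

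*Protocol article*

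**What the plan says.** In the Protocol article, Sample, eligibility needs any one of five alternatives:

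- Two are "tested HIV positive for the first time within the last 12 months or had not had an HIV care visit in the previous 6 months".
- Two more are "had a viral load of ≥200 copies/mL on her last lab test result or not currently prescribed ART medication".
- The last is "currently prescribed ART medication but did not rate her ability to take all her medications as excellent".

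Only one of the five requires an unsuppressed viral load and only one requires being off ART.

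Random Assignment balances on age, race/ethnicity and "HIV care continuum status (linked, nonlinked to HIV care"; neither viral load nor ART prescription is a factor.

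Statistical Analyses takes 130 women, two-sided alpha 0.05 and power 0.80, and states a "minimum detectable odds ratio of 2.98 for linkage/uptake of ART and achievement of an undetectable viral load". Table 2 scores both outcomes as status: prescribed ART or not, and above or below 200 copies/mL. It names no denominator of women without the outcome at baseline. The multivariate model has arm, self-reported exposure and time, with observations nested in participants. The only further covariates named are sociodemographic. The Discussion describes the trial's aim as one "with the ultimate goal of achieving viral suppression".

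**The concern.** Three things that the article itself fixes do not fit together: the labels in the power sentence (uptake, achievement), the scoring in Table 2 (status), and the number (all 130).

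A woman diagnosed 11 months ago who is in care, on ART and below 200 copies/mL meets the recent-diagnosis route. Every woman who enters by the last route is on ART by definition, and she may be suppressed. Such women start at 1 on the ART row, and on the viral-load row if suppressed. They can stay at 1 or fall to 0, but they have no room to gain. The linked/nonlinked factor does not separate them, because a linked woman may be suppressed or not.

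Viral suppression is the stated desired outcome. If many women have it at entry, an unadjusted comparison by arm loses power, and a null result could not tell texts that do not work from a ceiling.

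**Working it through.** **Inputs from the article.** Arms of 61 and 69, two-sided alpha 0.05, power 0.80, odds ratio (OR) 2.98.

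**Assumptions, because the article gives none of these.** Share *s* suppressed at entry; control rate of suppression among the rest, 0.25; control maintenance rate *m* among those already suppressed; effect of the texts on maintenance. A single follow-up time is compared, with no attrition.

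**Formulas.** Treated rate from control rate: p1 = OR·p0 / (1 − p0 + OR·p0). Power = Φ[(|p1 − p0| − 1.96·√{p̄(1 − p̄)(1/69 + 1/61)}) / √{p0(1 − p0)/69 + p1(1 − p1)/61}], where p̄ is the rate over both arms.

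**Step 1: the plan's own figure.** Solving for the OR that gives 80% power with 69 and 61 returns 2.98 at a control rate of about 0.196, and again at about 0.574. Elsewhere it is 3.73 at 0.10, 2.71 at 0.40 and 3.72 at 0.70. So 2.98 is attainable, but it cannot be confirmed without the control rate.

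**Step 2: no effect on maintenance, m = 0.90 in both arms.** Among unsuppressed women, 0.25 with OR 2.98 becomes 0.498. For s = 0.5:

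- control = 0.5 × 0.90 + 0.5 × 0.25 = 0.575
- treated = 0.5 × 0.90 + 0.5 × 0.498 = 0.699
- pooled OR = (0.699/0.301) / (0.575/0.425) = 1.72
- power = Φ[(0.124 − 1.96 × 0.0847) / 0.0836] = Φ(−0.50) = 31%

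| Share suppressed at entry | Pooled OR | Unadjusted power, all 130 | Power in unsuppressed women only |
|---|---|---|---|
| 0% | 2.98 | 84% | 84% (n=130) |
| 30% | 2.02 | 51% | 69% (n=91) |
| 50% | 1.72 | 31% | 55% (n=65) |
| 60% | 1.60 | 23% | 46% (n=52) |

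**Step 3: vary the effect on maintenance, s = 0.5.** The stratified column is a Mantel-Haenszel comparison over two baseline strata (unsuppressed, suppressed). With w = n0·n1/(n0 + n1) in each stratum, it compares Σw(p1 − p0) with √Σw²p̄(1 − p̄)(1/n0 + 1/n1). Power in unsuppressed women alone is 55% in every row.

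| Control maintenance | OR on maintenance | Unadjusted power | Stratified power |
|---|---|---|---|
| 90% | 1 | 31% | 42% |
| 75% | 1 | 29% | 34% |
| 90% | 2.98 | 46% | 64% |
| 75% | 2.98 | 64% | 74% |
| 60% | 2.98 | 76% | 81% |

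Stratifying beats the unadjusted comparison in every row. Restricting to unsuppressed women is better than either when the texts do nothing for maintenance. It is worse than the unadjusted comparison once they help women whose maintenance is 75% or lower.

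**Step 4: detectable OR in the at-risk subset.** At a control rate of 0.25 it is 2.82 for 130 women, 3.42 for 91, 4.26 for 65 and 5.04 for 52.

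**The case against.** The strongest reply is that including these women is deliberate. The trial aims at the whole care continuum, including retention and adherence, and the message library covers adherence. A woman on ART who doubts that she can take it all is a direct target, and preventing her rebound is an intended benefit. Status at follow-up in all randomised women is a legitimate outcome for that aim. This stands, and it is why the fix keeps all 130.

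Three stronger readings are tempting, and the document supports none of them.

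- *These women cannot score the outcome.* They can. Table 2 scores status, so staying suppressed counts 1 and rebound counts 0.
- *The 2.98 is wrong because it ignores them.* No control rate is given. The second rate that reproduces 2.98, about 0.574, is almost the 0.575 of a sample that is half suppressed (Step 2), so the figure may already describe a mixed sample. Even then, a pooled OR of 2.98 with no effect on maintenance would need an OR of about 7.1 in unsuppressed women.
- *The confirmatory test must be restricted to unsuppressed women.* Step 3 shows that this is a trade-off. At 50% suppressed and 75% control maintenance with OR 2.98, the unadjusted comparison has 64% power against 55% in the subset.

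It can also be said that outcomes are contrasted at baseline and each follow-up, and that a baseline covariate may sit in an analysis plan not shown. Both are fair. The missing covariate alone would be no finding. The point rests on the labels, the scoring and the number that the article does state.

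**Conclusion.** The concern holds in a limited form. The entry routes admit women already suppressed and on ART. The power sentence names uptake and achievement in all 130, while Table 2 measures status, so achievement and maintenance are mixed and an unadjusted comparison meets a ceiling.

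The loss could be large or small. With half suppressed at entry and a 25% control rate in the rest, unadjusted power for OR 2.98 runs from about 30% with no effect on maintenance to 46%, 64% or 76% with the same OR on maintenance and control maintenance of 90%, 75% or 60%. The share suppressed, both control rates and the maintenance effect are assumptions. The repeated-measures model could do better or worse than this single-time calculation. No arithmetic error in 2.98 is shown. The same reasoning applies to the ART outcome, for which no separate figures were worked.

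**What to change.** 1. Keep all randomised women in the comparison by arm of status at follow-up. Stratify by, or adjust for, baseline viral load (below 200 copies/mL, versus 200 or more or no suppressed result) and baseline ART prescription.
2. Pre-specify results by arm separately for women unsuppressed, or not on ART, at baseline (achievement, uptake) and for women already suppressed, or on ART (maintenance). Both groups are defined by status before randomisation, so the randomised comparison is preserved.
3. Reword the power sentence to match the status scoring, state its assumed control rate, and add the detectable OR for the at-risk number.

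Cost: wording and a little more analysis. The article plans contrasts of these outcomes at baseline, so the data should be at hand, and it states that primary analyses start only after follow-up ends. The detectable OR for the at-risk group will look less favourable. An adjusted OR is also a different quantity from an unadjusted one: at 50% suppressed and 90% control maintenance, an OR of 2.98 in both strata pools to 2.01. The plan should say which is meant.
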